### Data and safety monitoring

An independent data and safety monitoring board comprising cardiovascular surgeons, anesthesiologists, and statisticians will oversee all aspects of the study. The board will meet twice during the trial to monitor safety. It will make recommendations on study progress and performance, identify any major adverse outcomes or AEs due to the therapy, and give advice regarding whether the study should continue or if there should be a protocol change.

In this study, AEs are defined as any negative or unintended clinical manifestations that occur after the start of the study, regardless of medication. Any unexpected symptoms and signs, feelings of discomfort, or occurrence of AEs in patients during the trial will be recorded using medical diagnostic terminology on a case report form with detailed symptoms, time of occurrence, duration, severity, possible causal relationships, actions taken, results, and other relevant information. If an AE occurs, the patient will be monitored until their AE disappears. A follow-up investigation will be conducted, and the results will be recorded in case the intervention is halted due to the AE. The chief principal investigator ([name]) is responsible for reporting all AEs to the board and the regulatory authorities within 24 h.

The following are possible safety events relating to the intervention:decrease of eGFR by ≥50%Scr doubled since the last blood testprogression to CKD stage Vserious cardiovascular or cerebrovascular eventsheart rate < 40 bpmany unexpected event that the investigator believes could be attributed to the intervention

SAEs include any of the following:fatal or life-threatening complicationsdeath or persistent or significant disabilityhospitalization or significant medical intervention to prevent a serious outcomeany events that investigators examine are significant hazards or harm to the participants

Stopping rules for the trial:If an insufficient number of patients is enrolled.If the allocation codes are leaked during the trial or if more than 20% of the envelopes with emergency plans are opened, which would mean that the blinding has been nullified.Occurrence of SAEs that are likely to be related to the intervention drugs in the trial, which may indicate there are serious problems with the safety of the drug.

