Urine test	×	×	×	×	×	×	×	×	×
Stool routine and occult blood test	×	×			×			×	×
Liver function (ALT, AST, γ-GT)	×	×			×			×	×
Electrocardiogram	×	×						×	×
Other data									
Adverse events			×	×	×	×	×	×	
Allocation		×							
Drug distribution		×	×	×	×	×	×		
Drug recycling			×	×	×	×	×	×	
Drug count			×	×	×	×	×	×	
Research conclusion								×	×

Each visit allows a window of 3 days

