### Outcomes

The primary outcome of this trial will be the eGFR using the CKD Epidemiology Collaboration formula [21]. Secondary outcomes include changes in TKV, Scr, blood urea nitrogen (BUN), TCM symptoms, and pain. A composite outcome looks at the incidence rates of all possible safety events between two groups. AEs will be monitored throughout the trial and several biological indicators (blood and urine tests, electrocardiograms, and liver function test) will also be closely watched.

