### Data entry and quality control of data

Participant adherence to the protocol will be monitored by interviews at study check-up visits, which will promote retention and completion of follow-up assessments.

After verification of the content of the written case report forms, the data will be input independently into a database by two full-time research staff. To maintain data quality, all investigators will receive centralized training before the trial begins. Personal information (such as name, age, gender, ID number, date of birth, home address, contact information) will be kept in a locked storage unit according to standard guidelines. The quality control of the data will be assessed by the data and safety monitoring board three times at each trial site. The board will check that study procedures have been followed correctly according to the approved protocol. They will compare the data in the database with the source documents to evaluate its accuracy, completeness, and authenticity. The data and safety monitoring board will meet when the first participant enrolls, when 50% of the participants have been recruited, and when the last participant enrolls.

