### Trial status

The research strategy and study protocol were developed between October 2017 and June 2019. From October 2018 to July 2019, patients were screened and TKV was measured by MRI 24 weeks before the baseline. The follow-up visits and data analysis will take place from July 2019 to December 2020.

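### Table 2 schedules no adverse-event enquiry at week 48 although the text promises monitoring throughout the trial, and the safety board's meetings are given as two in one section and three enrolment-linked ones in another

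*Protocol article*

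**What the plan says.** **Adverse events.** The Abstract (Methods/design) and Outcomes have adverse events followed for the whole trial; in the words of Outcomes, "AEs will be monitored throughout the trial". Data and safety monitoring adds that "AEs are defined as any negative or unintended clinical manifestations that occur after the start of the study, regardless of medication" and that "If an AE occurs, the patient will be monitored until their AE disappears". Trial design sets 24 weeks of treatment followed by 24 weeks of follow-up. In Table 2, the row labelled "Adverse events" carries six marks, at visits 3 to 8, and none at visits 1, 2 or 9.

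**Safety board.** Data and safety monitoring states: "The board will meet twice during the trial to monitor safety". It gives no dates. Data entry and quality control of data says of the same board that it "will meet when the first participant enrolls, when 50% of the participants have been recruited, and when the last participant enrolls". The same section also says: "The quality control of the data will be assessed by the data and safety monitoring board three times at each trial site".

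**Calendar.** Trial status reports: "From October 2018 to July 2019, patients were screened". That screening MRI was done 24 weeks before baseline.

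**The concern.** Sites generally work from the schedule table. Followed as written, Table 2 puts no adverse-event question to the participant after week 24, and it has no visit between weeks 24 and 48. Outcomes makes the between-group incidence of safety events a composite outcome. Some events listed under Data and safety monitoring, namely serious cardiovascular or cerebrovascular events and unexpected events attributed to the intervention, are found by asking and not by a blood test. They could go unrecorded for half of the 48 weeks after randomisation.

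On the board, two sections give different counts, and the only timing stated anywhere follows enrolment. Enrolment milestones say little about how much treatment has been given. That matters more here because consent at visit 1 comes 24 weeks before allocation at visit 2.

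**Working it through.** **1. The adverse-event row.** Table 2 has nine visit columns. The row is marked at visits 3, 4, 5, 6, 7 and 8 (weeks 4, 8, 12, 16, 20 and 24) and is empty at visits 1, 2 and 9. Neighbouring rows (liver function, ECG, research conclusion) do carry a mark at visit 9, so the blank does not look like a lost column. Post-randomisation time without a scheduled enquiry: 48 − 24 = 24 weeks.

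**2. What week 48 still captures.** I take the composite to be the list of possible safety events in Data and safety monitoring.

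| Listed event | Scheduled source at visit 9 |
|---|---|
| eGFR fall of at least 50% | renal function |
| creatinine doubling | renal function |
| CKD stage V | renal function |
| heart rate below 40 bpm | vital signs, ECG |
| serious cardiovascular or cerebrovascular event | no scheduled enquiry |
| unexpected event attributed to the intervention | no scheduled enquiry |

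Liver, blood, urine and stool tests are also marked at visit 9. The gap therefore lies in clinical events, not in laboratory safety.

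**3. Board meetings.** One section gives two meetings, for safety, undated. The other gives three, at the first enrolment, 50% recruitment and the last enrolment. No sentence says whether the two are among the three or separate from them.

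**4. Exposure at the three dated meetings.** Assumptions: the article gives only months, so I take 1 October 2018 to 31 July 2019 as the outer bounds, 303 days or 43.29 weeks; 72 participants are evenly spaced, 43.29/71 = 0.6097 weeks apart; there is no dropout. If *T* is the meeting time, *t* a participant's enrolment time and *L* the lag from enrolment to treatment, then

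share = Σ min(max(*T* − *t* − *L*, 0), 24) / (72 × 24), with denominator 1,728 weeks.

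*Enrolment means screening (L = 24), last meeting.* The earliest participant has 43.286 − 24 = 19.286 weeks of treatment, and 32 participants have started: 32 × 19.286 − 0.6097 × (0 + 1 + … + 31 = 496) = 617.1 − 302.4 = 314.7; 314.7/1,728 = 18%. Nobody has completed 24 weeks.

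*Enrolment means randomisation (L = 0), last meeting.* 32 participants have completed, giving 32 × 24 = 768 weeks. The other 40 contribute 0.6097 × (0 + 1 + … + 39 = 780) = 475.6. Total 1,243.6; 1,243.6/1,728 = 72%. Completers: 32/72 = 44%.

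*Enrolment means randomisation, 50% meeting.* 0.6097 × (0 + 1 + … + 36 = 666) = 406.1; 406.1/1,728 = 23.5%.

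Brackets give the range for recruitment over 26 to 52 weeks:

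| Meeting | Enrolment = screening | Enrolment = randomisation |
|---|---|---|
| First participant | 0% | 0% |
| 50% recruited | 0% (0 to 0.3%) | 23.5% (14 to 28%) |
| Last participant | 18% (0.4 to 31%) | 72% (54 to 77%) |

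**5. The last participant.** Screening on 31 July 2019 puts baseline at 15 January 2020, week 24 at 1 July 2020 and week 48 at 16 December 2020. On either reading that participant's whole treatment period comes after the final dated meeting.

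**The case against.** The strongest reply is that the text already covers what the table omits. Several statements agree that adverse events count from the start of the study, are recorded during the trial and are followed to resolution. Against them stands one blank cell. All adverse events go to the board and the regulators within 24 hours, and Blinding has emergency unblinding reported to the safety board. The three milestone meetings sit in the data-quality section and match the three quality-control assessments per site, so two safety meetings plus three quality-control meetings is a plausible plan. Detailed board timing is also charter material that an article may condense.

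Much of this stands, and it rules out three stronger readings that a reader might infer:

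- *That weeks 24 to 48 contribute nothing to the safety comparison.* Renal function, vital signs and ECG at week 48 cover four of the six listed components, and no text restricts the composite to weeks 0 to 24.
- *That the rule on stopping for drug-related serious events has no scheduled review behind it.* Two meetings are expressly for safety and advise on continuation. Their dates are unstated, so the enrolment timing cannot be attributed to them.
- *That the board's last meeting sees little or no completed treatment.* This holds only if enrolment means screening. If it means randomisation, about 44% of participants have completed treatment (8 to 54% over the recruitment range above).

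The reply does not remove the contradictions. Prompt reporting starts only once the site learns of an event, and the table schedules no question that would bring it to light. The split between safety and quality-control meetings is a reader's reconstruction, and the sentence listing the three meetings is not limited to quality control.

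**Conclusion.** Both inconsistencies are confirmed from the article's own text.

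First, scheduled adverse-event enquiry covers 24 of the 48 post-randomisation weeks in Table 2, against the whole trial in the text. What is at risk is the ascertainment of clinical events in follow-up; laboratory and ECG surveillance continues.

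Second, the board meets two or three times depending on the section. The only dated meetings begin with no exposure and end before the last participant is treated. How much the final one sees is uncertain, about 18% or about 72% of planned treatment weeks, and depends on what enrolment means and on uniform recruitment over the assumed 43 weeks.

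This concerns the completeness of safety data and the clarity of oversight. It does not touch the sample size or the primary eGFR analysis.

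**What to change.** 1. In Table 2, mark adverse events at visit 9, worded as events since the last contact, so that the table agrees with the Abstract, Outcomes, and Data and safety monitoring.
2. State in Outcomes that the safety composite covers weeks 0 to 48. Because the definition counts events from the start of the study while visits 1 and 2 are also blank, say when recording begins.
3. Replace the two board descriptions with one schedule giving the number, purpose and timing of meetings. Say which are for safety and which for data quality, and define enrolment as screening or randomisation. Tie at least one safety review to accrued treatment exposure and not to enrolment.

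The cost is a few questions at a visit already planned, wording in the protocol and board charter, and possibly one meeting held later. No extra visit or test is needed.

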### Data entry and quality control of data

Participant adherence to the protocol will be monitored by interviews at study check-up visits, which will promote retention and completion of follow-up assessments.

After verification of the content of the written case report forms, the data will be input independently into a database by two full-time research staff. To maintain data quality, all investigators will receive centralized training before the trial begins. Personal information (such as name, age, gender, ID number, date of birth, home address, contact information) will be kept in a locked storage unit according to standard guidelines. The quality control of the data will be assessed by the data and safety monitoring board three times at each trial site. The board will check that study procedures have been followed correctly according to the approved protocol. They will compare the data in the database with the source documents to evaluate its accuracy, completeness, and authenticity. The data and safety monitoring board will meet when the first participant enrolls, when 50% of the participants have been recruited, and when the last participant enrolls.

### Ethics approval

This study has been approved by the international review board of each participating hospital. The trial was registered with the Chinese Clinical Trials Register (ChiCTR-INR-16009914) on 11 November 2016 (http://www.chictr.org.cn/showproj.aspx?proj=16783). Only clinicians with relevant qualifications will act as principal investigators. Written informed consent for the collection and use of participant data and biological specimens will be obtained from individual participants or authorized surrogates prior to enrollment. Personal information about potential and enrolled participants will not be disclosed to any third party before, during, or after the trial.

YNF is a combination of 17 herbal ingredients, which have a synergistic effect of nourishing the kidneys and spleen and alleviating blood stasis according to preclinical study evidence [14]. It is recommended for treating a variety of indications, including abdominal mass, soreness and weakness of the waist and knees, pain or tingling in the back, fatigue, cold or numbness of limbs, and mental listlessness. The potential mechanism of YNF in the treatment of ADPKD needs to be further explored. It has been reported that some of the herbs in YNF have pharmacological effects, such as inhibiting platelet and erythrocyte aggregation and improving the microcirculation [26, 27], relieving pain [28], anti-inflammation [29], anti-fibrous tissue proliferation [30, 31], anti-oxidant [32, 33], and anti-tumor [34] activities. Such activities may contribute (1) to the inhibition of cyst growth and cell proliferation, (2) to reducing the compression of the renal parenchyma, which is good for relieving ADPKD-related pain, and (3) to down-regulating Scr and BUN levels to improve renal function. Understanding which ingredients of YNF alleviate the symptoms of ADPKD requires further research. YNF has been used in clinical practice for several years and no safety concerns have been raised. The common adverse effects of YNF, such as diarrhea and increased urine output, appear to be mild and self-limited. The favorable safety profile of YNF increases its acceptability with the general population.

In view of the current evidence base, we have designed this placebo-controlled randomized controlled trial to test the efficacy and safety of YNF for ADPKD patients with CKD stages III–IV with the spleen, kidney deficiency, and blood stasis syndrome. This protocol complies with the SPIRIT 2013 [35] statement and SPIRIT 2013 explanation and elaboration [36], which cover scientific, ethical, and safety issues (Additional file 1). For patients with ADPKD, the findings of this study may help to improve their clinical symptoms and renal function, and slow cyst growth. We expect that this trial may provide preliminary evidence for the efficacy of YNF in treating ADPKD, which would be useful for researchers, practitioners, and patients.

There are some limitations to this study. First, considering the longer term, it was not feasible to measure the rates of more clinically important outcomes, such as renal replacement therapy or transplant. Second, this study is being performed in Shanghai, China, and it is uncertain whether the relative effects of YNF would be similar in other ethnic groups. Third, which ingredients in YNF contribute to the treatment effect needs further research and exploration.

### Trial status

The research strategy and study protocol were developed between October 2017 and June 2019. From October 2018 to July 2019, patients were screened and TKV was measured by MRI 24 weeks before the baseline. The follow-up visits and data analysis will take place from July 2019 to December 2020.

## Data Availability

Does not apply.

## Abbreviations

ACEI: Angiotensin-converting enzyme inhibitor
ADPKD: Autosomal dominant polycystic kidney disease
AE: Adverse event
ALB: Serum albumin
ALT: Alanine aminotransaminase
ARB: Angiotensin receptor blocker
AST: Aspartate aminotransaminase
BID: Twice daily
BUN: Blood urea nitrogen
CKD: Chronic kidney disease
eGFR: Estimated glomerular filtration rate
EI: Efficacy indicator
ESRD: End-stage renal disease
hCG: Human chorionic gonadotrophin
mALB/Cr: Microalbumin/creatinine
MRI: Magnetic resonance imaging
PKD: Polycystic kidney disease
RBP: Retinol-binding protein
SAE: Serious adverse event
Scr: Serum creatinine
TCM: Traditional Chinese medicine
TKV: Total kidney volume
ULN: Upper limit of normal
V2R: Vasopressin V2-receptor
VAS: Visual analog scale
YNF: *Yinang* formulation
β2-MG: β2-microglobulin
γ-GT: Gamma glutamyl transpeptidase
